## Introduction

Atrial fibrillation (AF) is the most common sustained cardiac arrhythmia. Over the last 20 years, the number of new cases of AF diagnosed each year has risen by 72%, and now surpasses the four most common causes of cancer combined.^1^ Moreover, it is estimated that up to 35% of the disease burden remains undiagnosed,^2^ and 15% of strokes occur in the context of undiagnosed AF.^3^

Oral anticoagulants can reduce the risk of stroke by up to two-thirds in those with AF at higher risk of stroke,^4^ and international guidelines recommend their use in patients with AF at elevated thromboembolic risk.^5^ Early detection of AF may permit the initiation of oral anticoagulation to reduce embolic stroke risk,^4^ and early antiarrhythmic therapy to reduce the risk of death and stroke.^6^ Accordingly, early AF detection is a key cardiovascular priority in the UK National Health Service (NHS) Long Term Plan,^7^ and the European Society of Cardiology recommends opportunistic screening by pulse palpation or ECG rhythm strip in persons aged ≥65 years and systematic ECG screening in those aged ≥75 years.^8^

Furthermore, AF frequently develops due to, and in parallel with, other cardiovascular, renal and metabolic conditions,^9^ and individuals with AF are at an increased risk of major cardiovascular events in excess of stroke including ischaemic heart disease, heart failure, chronic kidney disease, peripheral vascular disease and death.^10^ Thus, AF screening, with or without AF diagnosis, maybe a key opportunity for holistic management of cardiometabolic risk factors and unhealthy lifestyle behaviours to reduce an individual’s risk of later adverse events beyond that of stroke prophylaxis alone.

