## Methods and analysis

### Data sources and permissions

The derivation dataset will be the Clinical Practice Research Datalink-GOLD (CPRD-GOLD) dataset. This is an ongoing primary care database, established in 1987, which comprises anonymised medical records and prescribing data contributed by general practices using Vision software. It contains data for approximately 17.5 million patients, with 30% of contributing practices in England, and represents the UK population in terms of age, sex and ethnicity.^16^ In order to contribute to the database, general practices and other health centres must meet prespecified standards for research-quality data (‘up to standard’).^16 20^

Recorded information includes patients’ demography, clinical symptoms, signs, investigations, diagnoses, prescriptions, referrals, behavioural factors and test results entered by clinicians, and other practice staff. All clinical information is coded using Read Codes.^21^ Extracted patients will have patient-level data linked to Hospital Episode Statistics (HES), Admitted Patient Care (APC) and Office for National Statistics (ONS) Death Registration. The CPRD dataset has been used to develop or validate a range of risk prediction models.^22^

The extracted dataset, including linked data, comprises all patients for the period between 2 January 1998 and 30 November 2018 from the snapshot of CPRD-GOLD in October 2019. Over this study period, the CPRD-GOLD dataset comprises approximately 2 million patients eligible for data linkage at an up-to-standard practice, with over 200 000 patients having a record of AF during follow-up.

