#### Quantification of the association between short-term predicted AF risk and long-term AF and other diseases

We will include all patients randomly assigned to the testing dataset in CPRD-GOLD by the Mersenne twister pseudorandom number generator, categorised as lower or higher predicted AF risk by the developed prediction model at baseline (point of entry to the study). For long-term AF risk, we will plot Kaplan-Meier plots for individuals identified as higher and lower predicted risk of AF to assess the event rate for AF censored at 10 years, and calculate the hazard ratio (HR) for AF between higher and lower predicted risk of AF using the Cox proportional hazard model with adjustment for the competing risk of death. This will inform us of whether short-term AF risk is also associated with long-term AF risk, and whether an individual who undergoes risk-guided AF screening should be considered for repeated AF screening at a later time point (eg, 1 or 5 years).

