For non-AF disease states, we will consider the initial presentation of a cardiovascular, renal or metabolic disease or death. This is because AF is not a disease in isolation and is known to be associated with a high risk of adverse clinical outcomes. To best characterise highly prevalent and morbid diseases, associated with the development or consequence of AF and that may be appropriate for prevention or targeted diagnostic pathways subsequent to AF screening (online supplemental figure 1),^9^ we will individually examine the following nine conditions: heart failure, valvular heart disease (and specifically aortic stenosis), myocardial infarction, stroke (ischaemic and haemorrhagic) or transient ischaemic attack, peripheral vascular disease, chronic kidney disease, diabetes mellitus and chronic obstructive pulmonary disease. These disease states have been further selected for investigation because interventions could be implemented and/or tested to reduce their clinical progression. We will also quantify the occurrence of death by any cause recorded in primary care or by death certification from the UK Death Register of the ONS, which will be mapped on to nine disease categories (online supplemental table 2). For each condition, a list of diagnostic codes from the CALIBER code repository, including from ICD-10th revision (used in secondary care) and Read coding schemes (used in primary care) will be defined comprehensively to identify diagnoses from EHRs. Incident diagnoses will be defined as the first record of that condition in primary or secondary care records from any diagnostic position. For the definition of new cases, we will exclude individuals for the analysis of each condition who had a diagnosis of that condition before the patient’s entry to the study. If no indication of a specific disease is recorded, then the patient will be assumed to be free from the disease. CPRD is a positive recording dataset, which reduces the likelihood of the non-recording of a clinically identified disease state.

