We will create Kaplan-Meier plots for individuals identified as higher and lower predicted risk of AF to assess the event rate for non-AF outcomes censored at 10 years. We will derive the cumulative incidence rate for each outcome at 1, 5 and 10 years considering the competing risk of death, as well as death at 5 and 10 years. For each specified outcome, we will calculate the HR between higher and lower predicted risk of AF using Fine and Gray’s model with adjustment for the competing risk of death. We will also report adjusted HR where the model is adjusted for age, sex, ethnicity and the presence of any of the other outcomes at baseline. As some of the outcomes have incidence rates that are strongly associated with age (eg, aortic stenosis) or differ by sex (eg, heart failure),^39 40^ we will conduct subgroup analyses of incidence rates for higher and lower risk individuals for each outcome by age group (30–64 years and ≥65 years) and sex. As some of the non-AF outcomes are more likely to occur in the setting of prevalent AF (eg, stroke or heart failure),^9^ we will also conduct a sensitivity analysis whereby people with incident AF during follow-up are excluded.

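### The AF-free sensitivity analysis removes whole people because of AF recorded after baseline, and with them non-AF outcomes that came before the AF

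*Protocol article*

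**What the plan says.** All of this is in the protocol article, in the section on predicted AF risk and long-term AF and other diseases, unless noted.

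- **Exposure and time zero.** People in the testing set are "categorised as lower or higher predicted AF risk by the developed prediction model at baseline (point of entry to the study").
- **Follow-up.** Kaplan-Meier plots are planned "to assess the event rate for non-AF outcomes censored at 10 years".
- **Main estimate.** The estimator is stated thus: "we will calculate the HR between higher and lower predicted risk of AF using Fine and Gray’s model with adjustment for the competing risk of" (the competing event named is death). Everyone stays in.
- **Reason for the sensitivity analysis.** "As some of the non-AF outcomes are more likely to occur in the setting of prevalent AF (eg, stroke or heart failure").
- **Rule.** "we will also conduct a sensitivity analysis whereby people with incident AF during follow-up are excluded".
- **Expected order of events.** The Introduction says that "AF frequently develops due to, and in parallel with, other cardiovascular, renal and metabolic conditions", and the outcomes were chosen as being "associated with the development or consequence of AF".

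The article nowhere limits the rule to outcomes after AF, censors at AF, or treats AF as a time-varying state.

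**The concern.** The reason and the rule do not match. The reason concerns outcomes that happen once AF is present. The rule acts on the person: anyone with AF at any point in follow-up leaves the analysis, with all their AF-free time and any stroke, heart failure or other outcome that came first. Those earlier outcomes are part of the AF-free association the analysis is meant to show, and the article itself expects some of these diseases to precede AF.

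The loss is also unequal. The two groups are defined by predicted AF risk, so if the model works at all, the exclusions fall mainly on the higher-risk group. People who die early have less time to have AF recorded and are more likely to stay in.

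This is the only analysis described that looks at the non-AF associations with AF taken out. If it attenuates the HR for reasons of selection, readers may credit AF with more of the association than is due to it.

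**Working it through.** The article gives no figure for this analysis, so there is none to reproduce.

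**1. How many people (orientation only).** Data sources and permissions gives about 2 million patients, "with over 200 000 patients having a record of AF during follow-up". With the 80:20 split, the testing set is 0.20 × 2 000 000 = 400 000, of whom about 0.20 × 200 000 = 40 000 (10%) have AF recorded. That count covers the whole 1998–2018 extract. The number removed is smaller if AF after year 10 does not count.

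**2. Assumed inputs.** The article gives no hazards. Assumed per year, constant, higher- versus lower-risk group: AF a = 0.025 v 0.005; non-fatal outcome o = 0.02 v 0.01 (true HR 2.0); death d = 0.03 v 0.01 (true HR 3.0). A quarter of people are at higher risk and follow-up is 10 years. After the outcome, the AF recording hazard becomes k × a. The HRs below are simulated person-time rate ratios, which under constant hazards estimate cause-specific HRs, not Fine and Gray HRs.

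**3. Share of pre-AF outcomes deleted.** An outcome at time u is deleted if AF is recorded afterwards, before death and year 10. The probability is

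ka/(ka + d) × [1 − exp(−(ka + d)(10 − u))],

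averaged over u with weight exp(−(a + o + d)u). For k = 3 the first factor is 0.075/0.105 = 0.714 (higher risk) and 0.015/0.025 = 0.60 (lower risk). After averaging, 30% and 7% of pre-AF outcomes are deleted.

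**4. Effect on a non-fatal outcome.**

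| k | Deleted, higher risk | Deleted, lower risk | HR, exclusion | HR, censoring at AF |
|---|---|---|---|---|
| 1 | 12% | 2.5% | 1.99 | 2.00 |
| 2 | 21% | 5% | 1.83 | 2.00 |
| 3 | 30% | 7% | 1.68 | 1.99 |
| 5 | 44% | 12% | 1.46 | 2.02 |

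At k = 1 the HR is intact because staying in the set depends only on AF and death times, which are then independent of the outcome. Earlier outcomes are still lost, which costs precision.

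**5. What a reader would see.** Suppose AF also doubles the outcome hazard. The all-patient HR is then about 2.15 and the HR before AF about 2.0, so the honest attenuation is small. Exclusion gives 1.84, 1.70 and 1.44 for k = 2, 3 and 5.

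**6. Effect on death.** With no link between outcome and AF (k = 1), a death at time t is retained with probability exp(−at). Put s = a + d and T = 10.

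- Retained deaths: (d/s)(1 − e^(−sT)).
- Retained person-time: (d/s²)[1 − e^(−sT)(1 + sT)] + T e^(−sT).
- Higher risk: 0.2308/6.818 = 0.03384. Lower risk: 0.09286/9.060 = 0.01025.
- Ratio: 0.03384/0.01025 = 3.30, against a true 3.0.

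Across k = 1 to 5, simulation gives 3.3 to 3.4 under exclusion and about 3.0 under censoring at AF.

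**7. A second assumed set.** AF 2% v 0.2%, stroke 1% v 0.15% (true HR 6.7), death 5% v 0.6%. For k = 1, 3 and 10, exclusion gives 6.7, 5.7 and 3.7; censoring gives 6.6 to 6.7. If the multiplier lasts only one year after the stroke, exclusion gives 6.5 (k = 3) and 5.8 (k = 10). The death HR at k = 1 is 9.1 against 0.05/0.006 = 8.3.

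**8. Where censoring is not clean.**

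- *Shared frailty* (variance 0.5 and 1.0; first set, k = 1): all-patient HR 1.97 and 1.93; censoring 1.90 and 1.81; exclusion 1.81 and 1.66.
- *AF recorded late* (second set; stroke risk 5-fold after AF onset, mean delay 1 to 3 years, 80% of undiagnosed AF found at the stroke): the true HR before onset is 6.7; exclusion gives 6.6 to 6.7 and censoring at recorded AF gives 7.0 to 7.6.

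**The case against.** The strongest reply has four parts.

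*It is one sensitivity analysis.* The main HRs, adjusted HRs, cumulative incidences and subgroup rates keep everyone, and the stated aim of quantifying the association is answered there. The article declares no mediation aim. This stands, and it limits the severity.

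*The size is assumed.* With k = 1 the non-fatal HR is unbiased, and the largest distortions need a multiplier that persists for years. This stands as to size. It does not remove the problem: the article itself says that AF arises from these diseases, and the shift in the death HR needs no such link.

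*Attenuation is conservative.* A reader might infer that the study would wrongly conclude that AF explains all the non-AF risk. The figures do not support that: every HR under exclusion stays above 1 (lowest 1.44). What can go wrong is the apparent amount due to AF. Nor is the rule conservative for death, which moves the other way.

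*Censoring has its own bias.* The Introduction says that 15% of strokes occur with undiagnosed AF. If AF is found because of a stroke it had already caused, exclusion rightly removes that stroke and censoring at the recorded date keeps it. In the late-recording scenario exclusion did better. This stands: censoring is not bias-free, and which rule is nearer the truth depends on why AF follows the outcome. A cause-specific HR also differs in kind from the planned Fine and Gray HR, so it needs its own all-patient comparator.

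**Conclusion.** The point holds as a moderate issue. The rule selects people on an event after baseline that is commoner in the higher-risk group, and it discards person-time and outcomes outside its stated reason. Non-fatal HRs are biased toward 1 where the outcome raises later AF recording; the HR for death, if analysed this way, is biased away from 1.

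Under the first assumed set, a non-fatal HR of 2.0 falls to between 1.99 and 1.46 and a death HR of 3.0 rises to 3.3 to 3.4. These figures are illustrations that rest on constant hazards chosen for the purpose.

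Two stronger readings should be avoided. One is that the aim on non-AF diseases is compromised; it is not, because the main Fine and Gray analysis retains everyone. The other is that 10% of the analysed people would be lost; that share describes the whole extract, not 10-year follow-up in the testing set after baseline exclusions.

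**What to change.** Replace the exclusion sentence with a rule of this kind:

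- Keep everyone from baseline and censor follow-up at first recorded AF, giving a cause-specific HR for the outcome before AF.
- Report it beside an all-patient cause-specific HR, so that the two can be compared directly.
- For cumulative incidence before AF, treat AF and death as competing events.
- Add a short check that also drops outcomes recorded at, or shortly before, the first AF record, with the window set in advance. This shows how much undiagnosed AF could matter.
- If the exclusion analysis is kept, report it only as a secondary check with this limitation stated.

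The cost is one or two sentences and a little code, with no new data, since dates of first AF are already needed for the AF outcome. The remaining weakness should be stated: recorded AF can lag onset, so some outcomes caused by AF may count as preceding it, and censoring at AF may be informative.

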#### External validation

The CHS dataset will then be used to externally validate the model performance to assess transportability. A lack of external validation hampers the implementation of prediction models in routine clinical practice.^41^ The prediction model will be saved, including the RF structure, predictor variables and outcome variable into a standalone file. The file will be passed onto the external international collaborators so that they can apply the model to their local external cohort to generate predicted probability of experiencing AF at 6 months for each patient. Then the predicted probability will be compared against the observed outcome in the external cohort to assess the performance of the model. Prediction performance will be quantified by calculating the AUROC, Brier score and by using calibration plots, and the same aforementioned clinical utility and subgroup analysis will be conducted. The performance of the prediction model will be compared with the CHA_2_DS_2_-VASc and C_2_HEST scores.

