To ascertain whether the prediction model is transportable to geographies outside of the UK, we will externally validate its performance in the Clalit Health Services (CHS) database in Israel. As a result of the National Health Insurance Law, Israeli citizens are required to enrol in one of four payer-provider health funds and receive free basic healthcare. CHS provides health insurance coverage to 4.8 million insured members and about two-thirds of the population aged >65 years. CHS is recognised globally as the primary source of evaluation of COVID-19 vaccinations and therapies.^23–26^ All clinical information is coded in International Classifications of Diseases, Ninth Revision (ICD-9). Receipt of vital status from the Ministry of the Interior ensures 100% follow-up of mortality. We will include participants insured by Clalit with continuous membership for at least 1 year before 1 January 2019: 2 159 663 patients with 4330 of them having a new incident of AF (AF and/or atrial flutter (AFl)) in the first half of 2019.

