#### Internal validation

We will evaluate the model performance using a validation cohort with internal bootstrap validation with 200 samples. The model will be applied to the testing dataset with the same predictor variables. The area under the receiver operating characteristic curve (AUROC) will be used to evaluate predictive ability (concordance index) with 95% CIs calculated using the DeLong method.^38^ Youden’s index will be established for the outcome measure as a method of empirically identifying the optimal dichotomous cut-off to assess sensitivity, specificity, positive predictive value and negative predictive value. We will calculate the Brier score, a measure of both discrimination and calibration, by taking the mean squared difference between predicted probabilities and the observed outcome. To assess the clinical impact of using prediction model as opposed to other risk prediction scores, we will calculate the case reclassification, non-case reclassification and overall net reclassification index at the risk threshold that equates to the average 6 months incidence rate in the cohort and conduct a decision curve analysis, which assesses across threshold probabilities whether the predictive model would do more benefit than harm. Calibration will be assessed graphically by plotting predicted AF risk against observed AF incidence and quantified using a calibration slope.

The same methods will be employed in subgroups by age (<65 years, ≥65 years, <75 years, ≥75 years), sex (women, men) and ethnicity (white, black, Asian, others and unspecified) to assess the model’s predictive performance across clinically relevant groups.

The performance of the prediction model will be compared with the CHA_2_DS_2_-VASc and C_2_HEST scores. The CHA_2_DS_2_-VASc score was originally developed to predict stroke risk in individuals with AF, and the C_2_HEST score for Asian people without structural heart disease.^19^ These algorithms are robust to missing data in routinely collected primary care EHRs and have been tested for AF risk prediction in European cohorts.^19^ Other algorithms that can only be applied to a minority of European primary care EHRs (Pfizer-AI, CHARGE-AF) will not be considered as they cannot be implemented at scale to inform AF screening.^17 27^

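### Cheap improvement, not an error: in CHS, show the NRI and decision curves after an intercept update as well as for the locked model, because both depend on the baseline risk carried over from CPRD

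*Protocol article*

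**What the plan says.** External validation describes the CHS work as a fixed sequence. The model is saved, and "The file will be passed onto the external international collaborators so that they can apply the model to their local external cohort". "Then the predicted probability will be compared against the observed outcome in the external cohort to assess the performance of the model". The named measures are these: "Prediction performance will be quantified by calculating the AUROC, Brier score and by using calibration plots". Then "the same aforementioned clinical utility and subgroup analysis will be conducted".

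Internal validation defines those utility analyses: case, non-case and "overall net reclassification index at the risk threshold that equates to the average 6 months incidence rate in the cohort", and a decision curve across threshold probabilities. It also names a calibration slope, which External validation does not repeat for CHS.

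No recalibration in CHS is mentioned. The only updating mentioned is in Ethics and dissemination, for a model already in clinical use. The article does not say whether, in CHS, the cohort whose average incidence sets the NRI threshold is CPRD or CHS.

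**The concern.** The NRI at a fixed risk cut-off and net benefit both compare a predicted probability with an absolute threshold. If every CHS prediction is too high or too low by a common factor on the odds scale, both measures change even when the ranking of patients and the relative effects of the predictors carry over perfectly.

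The article describes several differences that age, sex and diagnoses may not absorb:
- CPRD baseline is first entry to the dataset, in a study period from 1998 to 2018; CHS patients are assessed at the start of 2019.
- AF is found through Read codes, hospital ICD-10 codes and death causes in CPRD, and through ICD-9 codes in CHS.
- CHS uses its own predictor code lists and a chronic disease registry.
- UK ethnicity categories are replaced in CHS by population sector and a socioeconomic score.

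Some unexplained shift is therefore plausible. At stake is the reading of the CHS utility results under the third aim, transportability: they would not separate a model that needs a local intercept from one whose predictors work less well in Israel.

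**Working it through.** **Inputs from the article (Data sources and permissions).**
- CHS: 2 159 663 patients, "4330 of them having a new incident of AF" in the first half of 2019. 4330 / 2 159 663 = 0.2005% in 6 months, or 0.401% per year.
- CPRD: about 2 million patients, over 200 000 "patients having a record of AF during follow-up", so about 10% over the whole of follow-up. No 6-month incidence after first entry is given.

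**Can the article size the shift?** No. Mean CPRD follow-up is not stated. If it were the full 20.9 years, the crude rate would be 0.10 / 20.9 = 0.478% per year, a ratio to CHS of 0.478 / 0.401 = 1.19. If it were 10 years, the ratio would be (0.10 / 10) / 0.00401 = 2.49. These are averages over follow-up of an ageing cohort and may include some prevalent AF. They do not bound the rate in the 6 months after entry, which is what sets the model's baseline. Only the part of a rate gap that the predictors leave unexplained would miscalibrate the model.

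**Illustration (assumed).** Let the true CHS risk be logit(p) = a + s·z, with z standard normal. Solving for mean risk 0.2005% and AUROC 0.80 gives a = −6.916 and s = 1.194. The locked model predicts the true odds multiplied by k, and nothing else is wrong.

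With incidence π and threshold t:
- J = sensitivity + specificity − 1. For two risk categories the overall NRI is J(model) − J(comparator), so a fall in J is the fall in NRI against any comparator whose classification does not move.
- Net benefit = sensitivity·π − (1 − specificity)·(1 − π)·t/(1 − t).

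| k | Flagged at t = 0.2005% | Sens. | Spec. | J | Net benefit per 100 000, t = 0.2005% | Net benefit per 100 000, t = 1% |
|---|---|---|---|---|---|---|
| 1 | 28% | 0.724 | 0.724 | 0.448 | 89.9 | +18.9 |
| 1.2 | 33% | 0.773 | 0.670 | 0.444 | 88.9 | +18.0 |
| 2 | 50% | 0.881 | 0.505 | 0.386 | 77.3 | −0.3 |
| 2.5 | 57% | 0.914 | 0.431 | 0.345 | 69.1 | −18.8 |

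Check of the 1% column:
- k = 1: sensitivity 0.223, specificity 0.974. 0.223 × 0.002005 − 0.026 × 0.997995 × 0.010101 = 0.000447 − 0.000262 = 0.000185 (18.9 per 100 000 unrounded).
- k = 2: sensitivity 0.429, specificity 0.914. 0.000860 − 0.000867 = −0.000007 (−0.3 per 100 000 unrounded).

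AUROC is 0.80 in every row. An exact intercept update returns each row to k = 1.

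**Sensitivity of the illustration.**
- Direction: a 2-fold under-prediction lowers net benefit at 1% only from about +19 to about +12.
- AUROC: with k = 2, net benefit at 1% goes from +7.3 to −12.5 at AUROC 0.75, and from +37.5 to +20.8 at 0.85.
- Threshold: at the CHS average incidence the 2-fold loss is (89.9 − 77.3) / 89.9 = 14%, much milder than at 1%.
- Meaning of the NRI cohort: with k = 2.5 and the cut-off at a CPRD-level rate raised by the same factor (about 0.50%), 28% are flagged and J is 0.448, so the NRI loss is zero.

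**Precision of the update.** The intercept's SE is about 1/√4330 = 0.015, giving a 95% CI of about ±0.03 on the log-odds scale.

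**The case against.** The strongest reply is that nothing here is wrong. Applying the model unchanged is the proper external validation. If its absolute risks are off in CHS, low net benefit is a true result for the model as transported. AUROC does not move under a pure intercept shift and a calibration plot shows one, so the planned outputs together would reveal the cause. A recalibrated analysis may also sit in the full plan that a condensed article does not reproduce. All of this stands, which is why the point is an improvement.

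A reader might go further and infer that a plain difference in AF rate between the countries would be read as failed transportability. The article does not support that. It sets no pass or fail rule for transportability and does not make the utility results decisive. Its statement in Ethics and dissemination is that the model could be made available if performance and utility are shown; it does not say only then, and does not tie this to CHS. Nor do the crude rates show that the model over-predicts in CHS.

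Two technical objections also hold. The NRI figures assume that "at the risk threshold that equates to the average 6 months incidence rate in the cohort" means CHS incidence when applied there, and that the comparator scores' classification does not shift too. And a random forest has no intercept of its own and can return a probability of exactly 0, for which a logit is undefined. The update is therefore a recalibration of the model's output and needs a stated floor and ceiling.

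What the reply leaves open is that seeing a shift on a plot does not tell the reader what the NRI or net benefit would be without it. No output named in the article does.

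**Conclusion.** The point holds as a cheap improvement. As described, the CHS utility measures use the locked probabilities, so a baseline-risk shift and poor transport of the predictors would be mixed in them. Whether this matters depends on a shift whose size and direction the article does not allow one to estimate. Under the assumed normal linear predictor with AUROC 0.80, a 1.2-fold over-prediction is negligible (NRI loss under 0.01). A 2-fold one costs about 0.06 of NRI at the CHS incidence threshold and all net benefit at a 1% threshold. If the predictors explain the whole rate difference, the update changes nothing and the two sets of results coincide. It would be wrong to conclude that the plan mislabels a rate difference as failure, or that the locked analysis should be replaced.

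**What to change.** In External validation:
1. Keep the locked model as the primary external validation and as the basis for any statement about using the model unchanged.
2. Add a labelled secondary analysis that re-estimates only the intercept in CHS: a logistic model with the logit of the locked probability as offset and one free parameter, with a stated floor and ceiling for random forest probabilities of 0 or 1. Report that intercept with its CI.
3. Show the NRI and decision curves side by side, as locked and as updated. Utility that recovers after the update points to baseline risk. Utility that stays low points to the predictors or their relative effects, since one parameter does not correct a wrong slope.
4. State that the NRI threshold in CHS is the CHS 6-month incidence.

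The cost is a few sentences and one extra set of results from predictions and outcomes that CHS will already hold. The downside is that the updated results use CHS outcomes and are not a pure external validation, so they must be labelled. With 4330 events, optimism from one parameter is negligible. Fixing this in advance also prevents recalibration from looking like a rescue after a disappointing result.
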